**Figure 2 F2:**
[figure not shown]
Flow chart of participant recruitment and inclusion in the SOCRATES cohort. CB-PTSD, childbirth-related post-traumatic stress disorder; SOCRATES, Stress Of Co-parents Related to A Traumatic Experience of birth across Switzerland.

### Data collection

Data are collected from four complementary sources: (1) obstetric and neonatal clinical data from medical records, (2) self-administered online parental questionnaires, (3) a structured institutional survey completed by participating centres and (4) linkage with national hospital discharge datasets (Medical Statistics of Swiss Hospitals, which also include data from birth centres). Clinical data are recorded at baseline and include maternal medical and obstetrical history, pregnancy characteristics and complications, labour and childbirth management (eg, induction, analgesia, mode of childbirth), postpartum complications (eg, haemorrhage, infection), and neonatal outcomes such as Apgar score, birth weight and neonatal unit admission. Participants are invited to complete four online questionnaires, shortly after birth (baseline), and at 2, 6 and 12 months post partum. All questionnaires are provided in French, German, Italian and English. In parallel, a methodological collaboration was established with the Swiss-Peristat project (SNSF 222882), which aims to validate national perinatal care quality indicators. A subset of clinical data collected in SOCRATES will be used to estimate the accuracy of routinely collected hospital administrative data from the Swiss Federal Statistical Office.

### Outcome measures and instruments

Primary and secondary outcomes are measured using validated self-report instruments. The full list of instruments, respondents, domains and time points is detailed in table 1.

**Table 1 T1:** Domains, validated instruments and timing of data collection for mothers and co-parents in the SOCRATES cohort

Domain	Topic	Validated scale	Number of items	Respondents and time points				Ref.
				Childbirth	2 months	6 months	12 months	
Childbirth	Fear of childbirth	Fear of Childbirth Visual Analogue Scale (FOCP-VAS)	1	◯	/	/	/	^54^
	Childbirth experience	Questionnaire for Assessing Childbirth Experience (QACE SF)	5	◉	/	/	/	^48^
	Traumatic experience	Peritraumatic Dissociative Experiences Questionnaire (PDEQ)	10	◉	/	/	/	^49^
	Satisfaction with care	Behaviour of the Mother’s Caregivers–Satisfaction Questionnaire (BMC-SQ)	7	◯	/	/	/	^50^
Physical health	General health	Minimum European Health Module (MEHM)	1	◉	/	/	/	^55^
		EuroQol Visual Analogue Scale (EQ-VAS)	1	◉	◉	◉	◉	^45^
	Early recovery	Obstetric Quality of Recovery-10 (ObsQoR-10)	10	◯	/	/	/	^56^
	Fatigue	Fatigue Assessment Scale (FAS), short selection at 6 and 12 months	10	/	◉	◉	◉	^38^
	Urinary incontinence	International Consultation on Incontinence Questionnaire–Urinary Incontinence (ICIQ-UI)	3	/	◯	◯	◯	^40^
	Anal incontinence	Jorge and Wexner anal incontinence score	3	/	◯	◯	◯	^41^
	Pain	Pain Intensity derived from the Brief Pain Inventory (BPI)	1	◯	◯	◯	◯	^39^
	Premenstrual symptoms	Premenstrual Symptoms Screening Tool (PSST)	1	◯	/	/	/	^57^
	Pelvic floor symptoms	Pelvic Organ Prolapse Distress Inventory-6 (PoPDI-6)	3	/	/	/	◯	^58^
Quality of life	Quality of life	EuroQol 5-Dimension 5-Level (EQ-5D-5L)	5	◉	◉	◉	◉	^45^
	Satisfaction With Life	Satisfaction With Life Scale (SWLS)	5	◉	/	/	◉	^59^
	Well-Being	The WHO–Five Well-Being Index (WHO-5 well-being)	5	◉	◉	◉	◉	^46^
	Flourishing	Secure Flourishing Index	12	/	/	/	◉	^60^
Mental health	Post-traumatic stress disorder (PTSD)	City Birth Trauma Scale for mothers/for partners (CB-PTSD)	29/29	/	◉	/	/	^25^ ^30^
	Depression, anxiety	Edinburgh Postnatal Depression Scale (EPDS and EPDS-3A)	10	◉	◉	◉	◉	^61^
	Stress	Perceived Stress Scale-4 (PSS-4)	4	◉	◉	◉	◉	^62^
	Loneliness	UCLA-Loneliness Scale-3 (UCLA-3)	3	◉	◉	◉	◉	^63^
	Resilience	Brief Resilience Coping Scale (BRCS)	4	◉	/	/	/	^64^
	Suicidal ideation	Patient Health Questionnaire-9 (PHQ-9) – item 9	1	◉	◉	◉	◉	^65^
Sexual health	Sexual function	Female Sexual Function-6 (FSFI-6)	6	/	/	◉	◉	^42^
	Sexual well-being	Natsal Sexual Well-being measure (NATSAL SW)	13	/	/	/	◉	^44^
Parenting	Bonding	Mother-to-Infant Bonding Scale (MIBS)	8	/	◉	/	/	^66^
	Parenting confidence	Me as a Parent Scale (MaaPs-SF)	4	/	◉	◉	◉	^67^
	Relationship	Brief Coparenting Relationship Scale (B-CRS)	14	/	/	◉	/	^68^
Support	Couple satisfaction	Couple Satisfaction Index (CSI-4)	4	◉	◉	◉	◉	^69^
	Social support	Multidimensional Scale of Perceived Social support (MSPSS)	12	◉	◉	◉	◉	^70^
Lifestyle	Sleep quality	Pittsburgh Sleep Quality Index (PSQI)	1	◉	◉	◉	◉	^71^
	Sleep	Insomnia Severity Index (ISI-3)	3	◉	◉	◉	◉	^72^
	Eating and body image	Maternal Body Image and Eating Behaviours Scale (MBIEB-S), short selection	4	/	◯	◯	◯	^73^
	Body image	Maternal Postpartum Quality of Life (MAPP-QOL)	1	/	◯	◯	◯	^74^
	Physical Activity	International Physical Activity Questionnaire (IPAQ short form)	2	◉	◉	◉	◉	^75^
	Physical Activity	Global physical activity questionnaire (GPAQ)	1	◉	◉	◉	◉	^76^
Work	Work-Family Conflict	Work-Family Conflict Scale (ISSP)	4	/	•	◉	◉	^77^

◯: mother; •: co-parent; ◉: Both mother and co-parent.

SOCRATES, Stress Of Co-parents Related to A Traumatic Experience of birth across Switzerland.

To address the primary objective (1), the prevalence and severity of CB-PTSD at 2 months post partum is measured using the City Birth Trauma Scale.^25^ This 29-item instrument, aligned with DSM-5 criteria, demonstrated excellent internal consistency and test–retest reliability in postpartum samples.^26 27^ A version specifically adapted for co-parents is used where applicable, featuring slightly modified wording to reflect their non-birthing role while preserving the instrument’s conceptual structure and psychometric properties.^28^,^31^

To address objective (2), depression and anxiety symptoms are assessed from the perinatal period to 12 months using the Edinburgh Postnatal Depression Scale (EPDS).^32^ This 10-item screening tool provides good internal consistency, is widely used in postpartum populations and validated in all four languages.^33 34^ In addition to the total score, anxiety symptoms are explored using the EPDS-3A subscale, which comprises items 3, 4 and 5, and has been proposed as a brief indicator of postnatal anxiety.^35^ Suicidal ideation is assessed using the ninth item of the Patient Health Questionnaire-9.^36^

In line with objective (3), maternal physical recovery is measured at baseline using the Obstetric Quality of Recovery-10,^37^ a 10-item scale scored from 0 to 10, with a total range from 0 to 100. It showed good internal consistency and test–retest reliability. Additional physical outcomes (ie, fatigue, Fatigue Assessment Scale),^38^ pain (using a single-item Numeric Rating Scale, 0–10), derived from the Brief Pain Inventory,^39^ urinary incontinence (International Consultation on Incontinence Questionnaire-Urinary Incontinence)^40^ and anal incontinence (Jorge and Wexner Score)^41^ are assessed longitudinally using short, validated tools with proven reliability in postpartum samples.

To address objective (4), maternal sexual health is assessed at 6 and 12 months post partum using the short version of the Female Sexual Function Index-6,^42^ which evaluates six domains (desire, arousal, lubrication, orgasm, satisfaction, pain). This instrument has demonstrated good to excellent internal consistency in postpartum populations.^43^ The Natsal Sexual Well-being Measure^44^ with good test–retest reliability is also administrated at 12 months post partum to assess broader sexual well-being.

For objective (5), health-related quality of life and well-being are assessed with the EuroQol 5-Dimension 5-Level questionnaire (EQ-5D-5L)^45^ and the WHO-5 Well-Being Index,^46^ both validated and widely used. The EQ-5D-5L is a generic measure of health status covering five dimensions (mobility, self-care, usual activities, pain/discomfort and anxiety/depression), each with five levels of severity, and includes a EuroQol Visual Analogue Scale ranging from 0 to 100 to assess overall self-rated health.^45^ The WHO-5 Well-Being Index is a five-item instrument assessing psychological well-being over the previous 2 weeks, with scores ranging from 0 to 100. It has demonstrated a good internal consistency and a robust unidimensional structure.^47^ At 6 months, an open-ended question invites mothers and co-parents to suggest, hypothetically, what could be implemented to improve parental well-being after childbirth.

Objective (6) focuses on the influence of clinical practices (eg, induction, mode of childbirth, perineal trauma), structural characteristics (eg, staffing levels, care protocols, availability of support services) and perceived care quality on health outcomes. Women’s birth experiences are assessed using four items from the Questionnaire for Assessing the Childbirth Experience.^48^ The Peritraumatic Dissociative Experiences Questionnaire^49^ assesses dissociative symptoms during labour, while the Behaviour of the Mother’s Caregivers Satisfaction Questionnaire^50^ evaluates relational aspects of care. Institutional-level characteristics derived from the maternity unit survey will be incorporated, including care models, staffing levels and workload indicators, organisational practices, availability of clinical protocols and support services and quality assurance procedures.

To meet objective (7), maternal and neonatal hospitalisations from 1 year before to 1 year after birth will be identified through deterministic and probabilistic linkage with the national Medical Statistics of Hospitals database, providing frequency, timing and diagnosis codes.

To address objective (8), we will examine how social determinants, gender roles and societal factors shape postpartum health and well-being. Individual-level measures include questions on perceived financial strain, employment conditions, experiences of discrimination, social support, paternity leave, division of domestic, caregiving tasks and mental load, and perceived gender inequities in the postpartum period.

In addition to validated instruments, the SOCRATES questionnaires include a set of ad hoc questions and adapted items designed to capture sociodemographic characteristics, family context and relevant behavioural and structural determinants of health. These items were selected based on their use in large-scale population surveys and were adapted when necessary to the perinatal context. Occupations and education levels are coded according to the International Standard Classification of Occupations (first two levels) and the International Standard Classification of Education-2011, respectively. Several items were drawn and/or adapted from national and international studies, including the Swiss Household Panel (eg, civil status, division of domestic tasks, health insurance), the French National Perinatal Survey (eg, birth plan, preference for epidural analgesia), the French ELFE cohort (eg, perceived partner support), the Irish MAMMI cohort (eg, factors affecting sexual life in the postpartum period) and the European Social Survey (eg, household income perception). An adapted version of the International Physical Activity Questionnaire was also included, following Swiss and WHO guidelines. All questionnaires were reviewed by healthcare professionals, patient associations and researchers, and pilot-tested for clarity, inclusiveness and cross-cultural relevance by a panel of young parents during the development phase.

In addition to individual-level data, the study collects institutional-level data through a structured survey administered to participating maternity units and birth centres. As no standardised instrument was available to comprehensively capture organisational and contextual characteristics of maternity care in Switzerland, a questionnaire was specifically developed for the SOCRATES study, building on previous national surveys and expert input. The development process included iterative discussions with multidisciplinary experts, item refinement and pilot testing to ensure clarity, relevance and feasibility across different care settings. The survey is completed once per institution by a senior staff member with detailed knowledge of local organisation (eg, head midwife, clinical expert or nursing manager). It comprises a comprehensive set of items covering structural characteristics (institution type, level of care, birth volume), models of care (including midwife-led care), infrastructure and clinical activity. It further collects detailed information on workforce capacity (full-time equivalents, vacancies, absences, skill mix, experience), organisation of work (shift systems, on-call arrangements, workload) and availability of services such as psychological support, breastfeeding support and social care. In addition, the questionnaire documents clinical practices and protocols (eg, monitoring, labour management, adherence to national or international guidelines), quality assurance activities, training opportunities and postpartum care pathways. These data enable multilevel analyses linking institutional characteristics with individual health outcomes and care experiences, and allow exploration of contextual determinants of postpartum health at the system level.

When validated versions were not available in all study languages, questionnaires were translated by professionals and subsequently reviewed by clinicians and researchers involved in the study, as well as by native-speaking users, to ensure clarity, relevance and appropriateness of wording across contexts. This process therefore followed a multistep, pragmatic approach, broadly aligned with established recommendations for the translation of health-related questionnaires in multinational studies.^51^ Minor adaptations were made where necessary to reflect the perinatal context. Where applicable, the psychometric properties of selected instruments will be assessed within the SOCRATES cohort, focusing on key measures used in primary analyses. These evaluations may include internal consistency and construct validity, depending on the specific instrument and planned analyses.

### Data management

Study data are collected and managed using Research Electronic Data Capture (REDCap), a secure, web-based software platform hosted on encrypted servers in Switzerland.^52 53^ The platform complies with Swiss federal data protection legislation and institutional security standards. Each participating family (mother and co-parent) is assigned a unique study identifier at the time of consent, allowing linkage of maternal and co-parent data while ensuring pseudonymisation of clinical and self-reported data prior to integration. REDCap provides structured case report forms with built-in logic checks and real-time validation rules to minimise entry errors.

Clinical data are entered into the electronic case report form by trained local research staff at each participating site. Questionnaires are completed online by participants via secure, individual access links. Access to identifiable information is restricted to authorised personnel at the local site level and to the central data management unit (DAUnit), in accordance with role-based access permissions. An audit trail automatically records all data manipulations, modifications, and exports. The REDCap platform also supports role-based access control, automated data exports to statistical software (R, Stata, SAS) and daily system backups. The DAUnit ensures system monitoring, compliance and recovery protocols. Quality assurance processes include periodic internal data control procedures, logic consistency checks and cross-validation of selected variables across data sources (eg, comparison between clinical records and self-reported data) to identify inconsistencies. Data from national hospital discharge records will be linked in accordance with the protocol approved by ethics committees and the Swiss Federal Data Protection Authority.

### Statistical analysis and weighing procedure

Descriptive analyses will be conducted to summarise participants’ characteristics and outcomes. Associations between predictors and outcomes will be examined using multivariable regression models, accounting for potential confounders identified through literature review, clinical expertise and directed acyclic graphs. Sensitivity analyses will be performed to evaluate the robustness of the findings. Missing items will be imputed using standard procedures whenever relevant (eg, multivariate imputation by chained equations). All analyses will be carried out using statistical software such as R or Stata.

To ensure representativeness at the national level, we will apply a weighting procedure that includes the following steps. First, base design weights are computed to account for differences in participation across maternity care institutions. Second, raking is applied to align the weighted sample distribution with known population margins, using key sociodemographic variables (education, income, age, Swiss nationality and parity). Predictive models (eg, Random Forest, XGBoost, Support Vector Machines) are employed to impute missing values in these key variables before calibration. Third, non-response adjustment weights are estimated through logistic regression using region, parental origin, education, ethnicity, age, living conditions, institution type and number of pregnancies as predictors. Predicted response probabilities from this model are then used to construct inverse probability weights, such that respondents with a lower predicted probability of response receive larger weights. To prevent undue influence of extreme weights, trimming is applied at predefined thresholds. The final adjusted weights are then assigned to all observations for subsequent analyses.

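### Raking precedes the non-response weights and trimming, and no later calibration is described, so the final weights are not guaranteed to reproduce the national margins

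*Protocol article*

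**What the plan says.** The section 'Statistical analysis and weighing procedure' of the protocol article gives the purpose and an ordered list: "To ensure representativeness at the national level, we will apply a weighting procedure that includes the following steps".

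1. "First, base design weights are computed to account for differences in participation across maternity care institutions".
2. "Second, raking is applied to align the weighted sample distribution with known population margins". The raking variables are education, income, age, Swiss nationality and parity.
3. "Third, non-response adjustment weights are estimated through logistic regression". The model's eight inputs are listed in the same sentence: "using region, parental origin, education, ethnicity, age, living conditions, institution type and number of pregnancies as predictors". Then: "Predicted response probabilities from this model are then used to construct inverse probability weights".
4. Finally, "trimming is applied at predefined thresholds. The final adjusted weights are then assigned to all observations" for later analyses.

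No calibration is described after step 2. The section does not say whether step 3 models failure to join the study, loss after joining, or both. The abstract links weighting to representativeness and attrition; the strengths and limitations box links it to non-participation and attrition.

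**The concern.** Raking forces the weighted sample to match chosen population margins. The match belongs to that set of weights and that set of people. If some people then leave the sample, the remaining weights are multiplied by unequal factors and the largest are cut back, nothing keeps the margins in place.

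The primary objective is a prevalence intended to be nationally representative, so the weights act directly on the main estimate. They also carry a heavy load. 'Recruitment and participation' reports 2122 fully completed baseline questionnaires from 6680 births (2122/6680 = 31.8%), and 'Sample size and power calculation' anticipates 60% follow-up after that. Objective 8 concerns social inequalities, and income is the one raking variable with neither its own term nor a near-equivalent in the response model.

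**Working it through.** **Benchmark from the plan.** The article gives no figure for the weights. Its only usable yardstick is the ±1 point margin at 5% prevalence. With 1900 responses, 1.96 × √(0.05 × 0.95/1900) = 1.96 × 0.005 = 0.98 points, which agrees with the stated margin.

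**Raking variables against the response model.**

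| Raking variable | In the step 3 model? |
|---|---|
| Education | Yes |
| Age | Yes |
| Income | No; only through correlated predictors such as education and living conditions |
| Swiss nationality | By proxy (parental origin, ethnicity) |
| Parity | By proxy (number of pregnancies) |

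**Reading A: the baseline is raked and step 3 models attrition.** Upper-end illustration for income, with no help from correlated predictors. Assume a 25% low-income margin and response of 48% in that group against 64% in the rest (overall 0.25 × 0.48 + 0.75 × 0.64 = 60%). The low-income share among respondents becomes 0.12/(0.12 + 0.48) = 20%, a 5-point drift.

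**Reading B: step 3 acts on something that raking already corrected.** Assume a 20% low-education margin already matched, and response of 45% against 63.75% (overall 60%). Weighting again gives (0.2/0.45)/(0.2/0.45 + 0.8/0.6375) = 0.444/1.699 = 26%, a 6-point overshoot.

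**Simulation of the stated order.** Population 6680, five binary variables, 100 replicates. The response model held education, age, a nationality proxy (80% agreement) and a parity proxy (85% agreement). Living conditions, region, ethnicity and institution type were left out, so a fuller model could do better on income. Participation and response strengths are assumptions. Entries are mean deviations from the population margin in percentage points; a positive sign means that the group more likely to take part is over-represented.

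| Scenario | Education | Income | Age | Nationality | Parity |
|---|---|---|---|---|---|
| Attrition, after inverse-probability weights | 0.3 | 4.2 | 0.2 | 3.1 | 1.1 |
| Same, trimmed at 5th/95th percentiles | 1.1 | 4.9 | 0.7 | 4.0 | 1.5 |
| Attrition, trimmed at 1st/99th percentiles | 0.3 | 4.2 | 0.2 | 3.1 | 1.2 |
| Initial non-participation, trimmed at 5th/95th | −12.3 | −2.9 | −4.2 | −3.8 | −0.8 |
| Re-raked at the end, every scenario | 0.0 | 0.0 | 0.0 | 0.0 | 0.0 |

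The zeros in the last row follow by construction: they show that the margins hold, not that all bias is gone.

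**Effect on the prevalence.** For one binary margin, bias ≈ drift × risk difference between its two groups. A separate simulation (50% low-income margin, about 2950 at baseline, 60% follow-up, response model with education only, trimming at the 95th percentile) gave a final low-income share of 41.8% and a prevalence of 4.78% against a true 4.97%; a final rake gave 5.02%. Drift is 50 − 41.8 = 8.2 points and bias 4.97 − 4.78 = 0.19 points, so the implied risk difference is 0.19/0.082 ≈ 2.3 points. Applied to the 4.9-point drift above, the bias is 0.049 × 2.3 ≈ 0.11 points. Against the 0.98-point half-width these are 0.11/0.98 = 11% and 0.19/0.98 = 19%.

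**The case against.** Calibrating a baseline cohort and multiplying by an attrition weight is a recognised longitudinal method, and the abstract's mention of attrition makes that the natural reading. Sociodemographic items come from the questionnaires, so predictors such as living conditions would mostly be missing for women who never took part; this makes the initial non-participation reading less likely. The text also says that the procedure includes these steps, so a final calibration could stand in an unseen analysis plan. And raking after trimming can recreate large weights.

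Much of this stands, and it rules out several stronger conclusions that a reader might draw:

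- *Every step after raking moves the sample away from the margins.* Not so under attrition: the inverse-probability weights pull respondents back towards the raked baseline on modelled variables, to within 0.3 points for education and 0.2 for age.
- *Income-related attrition is not corrected at all.* The model has eight predictors, and several plausibly track income. The correction is partial and of unknown strength.
- *The plan corrects education and age twice.* That is one possible reading of an unspecified step; the text does not state it.
- *The prevalence will be materially biased.* The article gives neither response rates by income nor any association between income and childbirth-related PTSD, so even the direction is assumed.

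The objection does not remove the gap for income, nationality and parity, or the effect of trimming. A possible later step does not answer it either, because the published sequence passes directly from trimming to the final weights.

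**Conclusion.** The point holds as a moderate weakness in a stated analysis rule. Followed as written, the procedure does not guarantee that the final weights reproduce the national margins that they are meant to match. That follows from the order of steps and needs no assumed numbers.

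The size does rest on assumptions. On the more natural attrition reading, education and age should be close to their margins, while income, nationality and parity could be off by roughly 1 to 5 points, depending on the proxies and the trimming. On the initial non-participation reading the deviations could be larger. The illustrative prevalence bias of 0.1 to 0.2 points is small against the planned ±1 point and scales in proportion to an income-related risk difference that the document does not give. The matter is worth correcting because the remedy is cheap; it does not invalidate the primary estimate.

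**What to change.** - State which non-response step 3 models: initial non-participation, attrition at each wave, or both in separate models.
- Add income, Swiss nationality and parity to the attrition model. Raking already needs these values for every baseline participant, observed or imputed.
- Order the steps as base weight, non-response weight, trimming, then raking last on the mothers analysed at 2, 6 and 12 months separately. Alternate trimming and raking until the margins hold and the weights stay bounded.
- Do the same for co-parents where population margins exist. The article documents none specific to them; where none exist, limit the claim of representativeness accordingly.
- Report final weighted margins beside the population margins for each wave.

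The cost is a change of wording, a little more analysis work and possibly slightly more variable weights. No new data are needed, and the sample size is unaffected.
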